### Analysis

Our preliminary analysis will include presentation of participant demographic characteristics, service usage, acceptability of intervention approaches and self-reported sexual behavior within each of the three study arms using descriptive statistics (one-way and cross-tabular frequency tables and, for continuous variables, measures of central tendency). Measures of variability will account for repeated measures (multiple patients) and consequent correlation of variables (clustering) within each health facility. We will employ multiple imputation (MI) using chained equations to account for missing data. This procedure assumes that incomplete data arise from a missing-at-random (MAR) process, under which missingness is random conditional on observed covariables and observed outcomes rather than a missing-completely-at-random (MCAR) mechanism [43], thus making fewer assumptions about the nature of the missing data. We will conduct sensitivity analysis using weighted MI to evaluate the robustness of the MAR assumption [44].

Our primary analyses will employ an intention-to-treat (ITT) approach. We will employ logistic generalized estimating equations (GEE) to compare patient retention between intervention arms. We will also evaluate secondary outcomes (linkage, adherence and prevention behaviors) using an ITT analysis, as described above. We will employ GEE rather than mixed effects models as this approach allows us to estimate the effect of the intervention at the level of the population, rather than at the level of the individual. As our interventions will be implemented at the level of the health system, it is important to estimate the effect of the intervention at the level it is implemented [45]. Further, previous research has suggested that adjustment for confounding can improve the efficiency of estimates in the context of randomized trials [46]. We will thus conduct sensitivity analyses employing causal inference methods to account for any imbalance in distribution of site- and individual-level co-variables across study clinics. We will employ targeted maximum likelihood estimation [47], which allows estimation of both site- and individual-level co-variables, to minimize bias and improve efficiency of estimates of effect in the context of small sample sizes [48].

Our secondary analyses will employ a per-protocol approach to evaluate differences in primary and secondary outcomes. These analyses will resemble the intent-to-treat analyses described above, with the difference that individuals will be evaluated based on the number of minutes of intervention exposure they receive. As above, these analyses will account for the clustering of results within sites and include use of causal inference methods to adjust for potential confounding. These analyses will allow us to determine whether an observed effect of the intervention is limited due to inadequate implementation and whether there is a needed dosage for the interventions to successfully impact outcomes. This will also permit any accounting for contamination should an SOC participant also receive services at an intervention clinic (their intervention dosage can be included), though we do not believe this will be common based on distance between study clinics and experiences during the pilot study. Our primary and secondary analyses will employ robust standard errors as these are unbiased in a setting where the coefficient of variation is less than 0.20 [49]. Our sensitivity analyses will include computation of confidence intervals using bias-corrected sandwich estimators [49–51]. Stata, version 13, will be used to manage data and conduct the primary and secondary analyses; more complex sensitivity analyses will be conducted using R.

Finally, for the cost analysis, we will use the observed primary study outcome, retention in care to estimate the cost per person retained in each intervention arm. Costs will be summarized as total costs, cost per clinic and cost per individual enrolled in each intervention arm. Cost will also be broken out by pre- and post-implementation periods in order to assess incremental costs associated with intervention scale-up (each additional clinic added or individual enrolled). Efficiency will be measured as the cost per additional person retained in care for each arm of the study.

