The first strategy includes three types of messages to be sent to participants that will be delivered automatically from a central system based on their gender and clinical/ART status recorded on registration and enrollment forms and updated through clinical record extraction (Fig. 2). These three message types include the following:Behavioral Messages: These messages are sent on a biweekly (every other week) basis, for a total of 26 messages during the 1-year study period. Behavioral messages are designed to address four themes: HIV prevention (some of these messages are gender-specific); engagement in care; medication adherence (for those on ART) or awareness (for those not yet eligible for treatment); and healthy living, which includes messaging concerning alcohol/drug use, social support and safe disclosure, and health/nutrition.Care Reminder Messages: Participants are sent a message 3 days before any scheduled clinic visits, whether for ART refills, CD4+ or HIV viral load testing, or other routine care. Participants also receive a reminder message if they have missed a clinic visit by over 2 weeks, in line with South African guidelines [13]. Patients receive up to 6 messages (bi-weekly) following a missed appointment to encourage them to return to the clinic. Additionally, when a client has failed to present for a visit for 3 months, the study staff will alert the clinic that a client has been lost to follow-up.Two-way Messages: These are automated biweekly “check-in” messages that are sent from a central system; they also record participant responses and send a system alert to the team if a follow-up call to the participant is needed. Two-way messaging serves to maintain contact with the participant, provides a means of retention in the study and in care, and also is a probe to ensure that the participant is not defaulting on care and treatment or experiencing any difficulties that need to be addressed. The participant receives a request to “reply 1 if you’re good or 2 if you have a problem and need to talk.” If the participant responds “2,” project staff will receive an alert to call the client within the first business day after receiving the notification. If the participant does not respond to the check-in message within 24 hours, the participant receives the message a second time. If the participant has not replied to either message after 48 hours, the study staff will receive an alert to call the client. When staff call for either a “2” response or a non-response, they follow a protocol for referrals and are trained not to offer advice and counseling. Responding to two-way messages is free of cost for participants.

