Linkage to HIV care	CD4 drawn and results available at clinic within 3 months of testing HIV positive	Intake and Record extraction	Weekly (ART) bi-weekly (pre-ART)
	CD4 result received within 3 months of testing HIV positive	Survey data (self-report)	0 and 6 months
	Patients eligible for ART who initiate treatment within 3 months of CD4 staging	Intake and Record extraction	Weekly (ART)
		Survey data (self-report)	0, 6, and 12 months
Adherence to ART	Proportion taking 90 % and 100 % of pills in the past 30 days	Survey data (self-report)	0, 6, and 12 months
	Breaks in treatment during the previous six months (at least 4 days in a row)	Intake and Record extraction	Weekly (ART)
		Survey data (self-report)	0, 6, and 12 months
	Proportion of days covered (# of dispensed days of medication/# of days between refills)	Intake and Record extraction	Weekly (ART)
Prevention (transmission risk)	Number of unprotected sex acts by partner HIV status	Survey data (self-report)	0, 6, and 12 months

Because the volume and intensity of the intervention might vary, particularly in the PN arm, we will also capture intervention exposure or dosage as a secondary exposure measure. Dose (minutes) of intervention received will be used for per protocol analyses. In the PN arm, this will include recording client data on frequency and duration of in-person meetings and phone communications with the navigator. Delivery and response to SMS messages for both intervention arms will be recorded with a standard duration of exposure (for example, 30 seconds) for each message, including two-way messaging. Any phone or in-person follow-up to SMS messages will be recorded separately. Secondary outcomes include linkage to HIV care, adherence to medications, and transmission risk behavior, as described in Table 1.

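### The per-protocol analysis uses minutes of intervention received, which depend partly on care status and need not precede the outcome, so it cannot determine a needed dosage

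*Protocol article*

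**What the plan says.** The protocol article, under Measures, fixes the exposure: "Dose (minutes) of intervention received will be used for per protocol analyses". In the peer-navigation (PN) arm, "this will include recording client data on frequency and duration of in-person meetings and phone communications with the navigator". Text messages in both intervention arms "will be recorded with a standard duration of exposure (for example, 30 seconds) for each message, including two-way messaging". Phone or in-person follow-up prompted by a message is to be recorded separately; whether it counts towards dose is not said.

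Under Analysis, the secondary analyses repeat the intention-to-treat models for primary and secondary outcomes, except that "individuals will be evaluated based on the number of minutes of intervention exposure they receive". They are to account for clustering and use causal inference methods to adjust for potential confounding. The method named is targeted maximum likelihood estimation with site- and individual-level covariables. The authors say these analyses will let them determine whether an effect was limited by inadequate implementation and "whether there is a needed dosage for the interventions to successfully impact outcomes".

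Under Intervention, contact depends on attendance and response. "Participants also receive a reminder message if they have missed a clinic visit by over 2 weeks", and "Patients receive up to 6 messages (bi-weekly) following a missed appointment to encourage them to return to the clinic". A check-in left unanswered for 24 hours is sent again. A reminder precedes each scheduled visit and is triggered by the next-appointment date taken from the chart. PN participants get behavioural messages and appointment reminders on the same schedule, at least two navigator contacts a month for 12 months, and further contacts when challenges emerge.

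**The concern.** A dose-response analysis supports a causal reading only if the dose comes before the outcome and is not produced by it. Here the dose is a post-randomisation quantity with no stated time window, and the intervention's own rules let care status drive part of it. An association between minutes and retention could mean that more contact keeps people in care, or that being in or out of care changes the number of contacts. The planned model cannot tell these apart.

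At stake are two conclusions that the protocol promises: whether implementation was inadequate, and how much intervention is needed. Both could bear on scale-up. The Discussion already considers building parts of peer navigation into ward-based outreach teams, pending the findings.

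**Working it through.** No figure in the plan needs reproducing, because the point concerns the choice of exposure. The check has three parts.

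**1. Timing.** The passages set side by side:
- Retention is assessed at 6 and 12 months (Measures). Minutes in months 7 to 12 cannot affect 6-month retention, yet nothing excludes them.
- Linkage to care is judged within 3 months of diagnosis (Measures), but participants may enrol up to 1 year after diagnosis (Participant eligibility and recruitment). For anyone enrolled more than 3 months after diagnosis, linkage is settled before the first minute of intervention.

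**2. Message arithmetic, SMS arm.** Inputs: 0.5 min per message (the example under Measures), 26 behavioural messages, up to 6 messages after one missed appointment. Assumptions: 26 check-ins a year (every two weeks, as for the behavioural messages) and monthly visits for those in care.
- Behavioural messages: 26 × 0.5 = 13 min. Check-ins: 26 × 0.5 = 13 min.
- Added by disengagement: missed-visit messages up to 6 × 0.5 = 3 min; repeat check-ins up to 26 × 0.5 = 13 min.
- Added by engagement: pre-visit reminders 12 × 0.5 = 6 min; replies, if credited, up to 26 × 0.5 = 13 min.

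Compare a fully engaged participant with one who never replies and leaves after three pre-visit reminders (3 × 0.5 = 1.5 min):

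| What is counted | Engaged (min) | Disengaged (min) | Ratio |
|---|---|---|---|
| No replies, no pre-visit reminders | 13 + 13 = 26 | 26 + 13 + 3 = 42 | 42/26 = 1.62 |
| Pre-visit reminders, no replies | 26 + 6 = 32 | 42 + 1.5 = 43.5 | 43.5/32 = 1.36 |
| Pre-visit reminders and replies | 32 + 13 = 45 | 43.5 | 43.5/45 = 0.97 |

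These are extreme cases. Which of the two accrues more dose depends on what is credited.

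**3. Simulation with a true dose effect of zero.** Each setting used 500 simulated trials of one arm: 7 clinics × 42 participants, 50% retained (the retention that the sample-size section assumes for standard of care), and intra-cluster correlation 0.0225 applied on the logistic scale. The model was a logistic GEE with robust standard errors, adjusted for a measured baseline covariate that affects retention. Assumptions not in the documents: navigator contact averaging 40 min a month; reply rates of 30% to 90%, unrelated to retention and credited; monthly visits; 30% of retained participants with a missed visit; all non-retained participants receiving the full 6 messages. Repeat check-ins were not simulated.

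| Setting | Median OR per SD of minutes | Share with p < 0.05 |
|---|---|---|
| SMS, minutes independent of outcome | 1.00 | 12% |
| SMS, missed-visit messages only | 0.31 | 100% |
| SMS, plus pre-visit reminders that stop on leaving care | 1.11 | 23% |
| PN, contact never stops on leaving | 1.01 | 10% |
| PN, contact stops for 25% of leavers | 1.45 | 87% |
| PN, contact stops for 50% of leavers | 2.13 | 99.8% |
| PN, contact stops for all leavers | 7.11 | 100% |

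The 12% in the reference setting exceeds 5% because there are only 7 clusters. The sizes are illustrative. The result that matters is that associations in either direction arise with no effect of dose, and adjusting for a baseline covariate does not remove them.

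**The case against.** A reader might infer that dose-response must slope down in the SMS arm and up in the PN arm whatever the true effect, and that a defaulter in the SMS arm accrues about 60% more dose. The document does not support this. The 60% comes only from the first row of the message table, which leaves out pre-visit reminders and credited replies; with both counted, the ratio falls just below 1. The simulated SMS odds ratio likewise moves from 0.31 to 1.11 once pre-visit reminders are included. That leaving care ends navigator contact is nowhere stated. It is inferred from the monthly in-person meetings and from the 10% of pilot participants who moved away within 3 months. Phone contact is allowed, participants in difficulty may get more contact, and with no stopping the PN bias disappears.

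It can also be said that the exposure window and the adjustment set belong in the statistical analysis plan, which is not shown. The article does not say that minutes are summed over 12 months or that only baseline covariables are used, so a time-varying method is not ruled out. Reactive calls are already recorded separately. The analysis is secondary.

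These points remove any prediction of direction or size, but they leave the core standing. The article does not merely leave a detail open. It names the exposure, says that the models resemble the intention-to-treat ones, and states the causal conclusion. Adjustment for confounding, as described, does not undo dependence of the dose on the outcome process, and an unpredictable bias makes the result hard to interpret rather than safe.

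**Conclusion.** The concern holds in this form: minutes received are partly a consequence of care status and are not required to precede the outcome. The planned analysis therefore cannot determine a needed dosage or inadequate implementation. The messages triggered by missed visits and by non-reply, and the dependence of pre-visit reminders on an appointment date, are documented. Loss of navigator contact on leaving is plausible but inferred. Bias can run either way, and no size can be read from the document; the simulated odds ratios of 0.31 to 7.11 rest on the stated assumptions and cover one arm at a time. The label per-protocol is also wrong, since this is an exposure-response analysis. The change should be made, but it concerns secondary analyses only. The primary intention-to-treat comparison and its power are untouched.

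**What to change.** - For each outcome, define dose as scheduled contacts received in a window that ends before that outcome is assessed. One example is a landmark at 6 months among those still in care, relating contacts up to then to 12-month retention.
- Report reactive contacts separately: missed-visit messages, repeat check-ins and the calls that they trigger. They stay part of the intervention but are not counted in this dose.
- Do not run the dose analysis for outcomes settled before the dose accrues, such as linkage to care.
- Call it an exploratory dose-response analysis rather than per-protocol, and delete the claim that it will determine a needed dosage. Draw no firm conclusion on inadequate implementation from it.

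The cost is mainly wording, since contact forms and message-system records are captured continuously (Table 1). Early leavers drop out of the landmark analysis, so its result applies only to people still in care at the landmark. It remains observational and open to confounding, which is why the exploratory label is needed. The primary analysis does not change.

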### Sample size estimation

We aim to enroll 750 patients across the 18 participating clinics, with the goal of ensuring that each of the 18 clinics has at least 30 participants, and no site more than 55 to guarantee a well-balanced sample and minimize variability. We anticipate that approximately 20 % of the sample will discontinue study participation, largely due to extensive migration in the area. This estimate of attrition is grounded in on our pilot experience, during which 10 % of participants moved out of the area during a 3-month observation period. We therefore anticipate an evaluable sample of 600 participants over 1 year. Under the assumption that only 50 % of participants in the SOC clinics will remain in care [10, 38], this sample size will provide 80 % power to observe a 20 % to 23 % difference in patient retention at 12 months between the PN and SOC or SMS and SOC arms and a 17 % to 20 % difference between the PN and SMS arms. These estimates assume a two-sided alpha of 0.05 and a coefficient of variation of 0.15 to 0.20 or an intra-cluster correlation of 0.0225 to 0.04 based on a review of the recent literature around sample size estimation in large cluster randomized trials [52, 53].

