**Fig. 1 Fig1:**
[figure not shown]
Clinic allocation and participant enrollment. Notes: ^a^ Clinics were not eligible if they had a catchment area under 6,000 inhabitants, inadequate patient load to ensure recruitment targets (40 new patients to patient registers in the first 4 months of 2014), were pilot clinic sites (n = 4). ^b^ One clinic assigned to the SMS arm was under construction and has not opened as scheduled; as such, recruitment targets have been adjusted at the remaining SMS clinics. ^c^Participants are eligible if they are 18 or older, diagnosed with HIV within the last 12 months, receiving care at a study clinic, and willing to receive communication from study staff. Abbreviations used in the figure: No. = Number; PN = Peer Navigation; SMS = Short Message Service (i.e., Text Message); SOC = Standard of Care

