Although this trial will yield important data to drive programming in South Africa and surrounding countries, some limitations exist to potential inferences and the generalizability of the findings. Clinics selected for the study come from both peri-urban and rural areas; however, the selection area was limited to two sub-districts and included only those clinics with sufficient patient load to warrant inclusion. As a result, findings may not be generalizable to clients attending private clinics, to residents of other provinces, or to residents of large metropolitan centers or very rural areas where clinics have limited HIV patient load. Additionally, while trial participants are being systematically invited to participate and should represent the current patients undergoing HIV testing and receiving services at the clinics, the study population is not representative of the large number of residents who do not present for testing, which comprise approximately 35 % of the national adult population [57].

Results will provide crucial information regarding the efficacy of two complementary intervention strategies, with the recognition that one intervention (SMS) is less resource intensive but also less flexible in terms of the patient barriers to care that it can address. This trial is powered to compare retention outcomes at 12 months between the SOC and both the SMS and the PN intervention. This is an opportunity to estimate not only intervention efficacy but also incremental efficacy from the base SMS model to an enhanced peer navigation model with patient reminders (which could be generated either from an automated SMS system or directly from a peer navigator). In the future, an exploration of targeted interventions, or whether a more intensive intervention (PN) could be targeted to the clients with more personal barriers who require additional support, is needed. In addition, knowledge of whether the less intensive model of SMS would be sufficient for those who need reminders but do not experience major barriers, such as fear of disclosure or substance use, is also needed.

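### The stated 80% power against standard of care makes no allowance for having only four control clinics; on a true 5% test it is about 71-77%

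*Protocol article*

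**What the plan says.** The Sample size estimation section claims 80% power for a 20 to 23 point "difference in patient retention at 12 months between the PN and SOC or SMS and SOC arms", and gives "a 17 % to 20 % difference between the PN and SMS arms". It assumes 600 evaluable participants from 750 enrolled at 18 clinics, and that "only 50 % of participants in the SOC clinics will remain in care". It continues: "These estimates assume a two-sided alpha of 0.05" and a "coefficient of variation of 0.15 to 0.20 or an intra-cluster correlation of 0.0225 to 0.04". It names no formula, no small-cluster correction and no reference rate for PN v SMS.

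Clinic selection and randomization gives seven clinics to each intervention and four to SOC. The Fig. 1 notes report that "One clinic assigned to the SMS arm was under construction and has not opened as scheduled", with recruitment targets moved to the other SMS clinics.

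The Analysis section plans logistic GEE with robust standard errors for the primary analysis and keeps bias-corrected sandwich intervals for sensitivity analyses. The Discussion concludes: "This trial is powered to compare retention outcomes at 12 months between the SOC and both the SMS and the PN intervention".

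**The concern.** Clinics were randomised, so the precision of a contrast with SOC is limited by four control clinics. With 10 or 11 clinics in a contrast, the between-clinic variance is itself poorly estimated. A normal reference then gives either a power figure that is too high or a test whose real error rate exceeds 5%. If the 80% is overstated, a null comparison with SOC would be read as stronger evidence against a 20 to 23 point benefit than the design can give. The CV and ICC raise a separate question: whether both describe the same between-clinic variance at the retention rates the trial hopes to see.

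**Working it through.** **Inputs.** Evaluable per clinic m = 600/18 = 33.3; SOC retention 0.50; two-sided alpha 0.05; ICC 0.0225 with 20 points and 0.04 with 23 points; clinics 7/7/4 planned, 7 PN, 6 SMS and 4 SOC open. Assumption: the six SMS clinics keep the arm's evaluable total, 33.3 x 7/6 = 38.9 each (38.9/0.8 = 48.6 enrolled, inside the stated maximum of 55).

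**Formula.** Variance of an arm proportion = p(1-p)[1 + (m-1)ICC]/(m x clinics). Power comes from the difference divided by its standard error (SE), referred to the normal or to the noncentral t.

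**Reproducing the stated figure, 7 v 4 clinics.**
- ICC 0.0225: design effect 1 + 32.33 x 0.0225 = 1.7275. SOC variance 0.25 x 1.7275/133.3 = 0.00324; intervention variance at 70% is 0.21 x 1.7275/233.3 = 0.00155. SE = 0.0692; 0.20/0.0692 = 2.889. Normal power 82.3%.
- ICC 0.04: design effect 2.293, SE = 0.0790; 0.23/0.0790 = 2.912. Normal power 83.0%.
- Solving for 80% power gives 19.4 and 22.2 points, which round up to the stated 20 and 23. For PN v SMS from a 50% reference (assumed) the result is 16.6-18.9 points, or 16.7-19.2 with a pooled variance, against the stated 17-20.

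So the plan's figures follow from its ICC and normal quantiles.

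**Allowing for few clusters.** The two values in a cell are for 20 points with ICC 0.0225 and 23 points with ICC 0.04.

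| Contrast | Normal | t, pairwise df | t, pooled df = 17 - 3 = 14 |
|---|---|---|---|
| PN v SOC (7 v 4) | 82.3 / 83.0% | df 9: 73.0 / 73.7% | 76.6 / 77.3% |
| SMS v SOC (6 v 4) | 81.5 / 81.8% | df 8: 70.7 / 71.1% | 75.7 / 76.1% |

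Differences detectable at 80% power:
- pairwise df: 21.7-24.7 points (PN v SOC) and 22.3-25.4 (SMS v SOC);
- pooled df: 20.8-23.7 and 21.0-24.1.

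**Does the planned test recover the 80%?** In a beta-binomial simulation (40,000 runs) the uncorrected robust z test rejected in 86% of runs at the stated SOC differences, but also in about 12% of runs under the null (about 9% for PN v SMS). A t test on clinic proportions held 5.0-5.4% under the null in the SOC contrasts, with power of 72-75%.

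**PN v SMS, 7 v 6 clinics, t on 11 df.** At 17 points/ICC 0.0225 and 20 points/ICC 0.04:
- reference 50%: 73.2 / 75.5%;
- reference 60%: 78.3 / 81.3%.

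**CV against ICC.** ICC = CV^2 x p/(1-p). At p = 0.50, CV 0.15-0.20 gives exactly 0.0225-0.04. At p = 0.70, CV 0.15 gives 0.0525; at p = 0.73, CV 0.20 gives 0.108. If the CV is the same in both arms, the arm variance is [CV^2 p^2 + p(1-p)/m]/clinics. For 7 v 4 at CV 0.15, SE = 0.0759 and 0.20/0.0759 = 2.636, so normal power is 75.1%; at CV 0.20 it is 71.6%. With t on 9 df these become 65.2% and 61.6%.

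**Effect of the unopened clinic.** Going from 7 to 6 SMS clinics takes SMS v SOC from 82.3 / 83.0% to 81.5 / 81.8% with normal quantiles, and from 73.0 / 73.7% to 70.7 / 71.1% with t. PN v SOC does not change on pairwise df.

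**The case against.** The strongest reply is that nothing has been miscalculated: the figures reproduce from the stated inputs, and normal quantiles match the planned GEE with robust standard errors, which has no t reference. The first part stands. This is an omitted allowance, not a slip of arithmetic. The second part does not rescue the claim. The section states a two-sided 5% level, and the uncorrected test keeps its power only by rejecting about 12% of the time under the null in the SOC contrasts. It does show that power and primary test must be corrected together; t-based power attached to a z-based test would also be a mismatch.

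The choice of degrees of freedom is also open. Pooled df give a shortfall of 3-4 points rather than 6-9, which is why both are reported.

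A reader might infer three stronger things that the article does not support:
- That the unopened SMS clinic breaks the calculation. With normal quantiles, 17 clinics and the arm total kept, power is still about 81-83%. The note also says only that opening was delayed.
- That power v SOC is really 58-65%. That needs t quantiles and a CV constant across arms, and the article does not say that the CV is constant.
- That PN v SMS is certainly short of 80%. At a 60% reference it is roughly at target.

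**Conclusion.** The point holds for the SOC contrasts. At the stated differences and ICC, a test with a true 5% level has about 71-74% power on pairwise df, or 76-77% on df pooled over 17 clinics, against the 80% claimed. The detectable differences are about 22-25 or 21-24 points instead of 20-23. This rests on equal clinic sizes within an arm, 50% SOC retention and the SMS arm keeping its total.

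The CV wording is a separate defect. If the CV is constant across arms, normal quantiles with 7 v 4 clinics give only 75% and 72%, and t gives less. PN v SMS cannot be settled without its reference rate. The unopened clinic costs about 1-3 points in the SMS contrasts, but the count of 18 clinics in the sample size section still has to be reconciled with the Fig. 1 note.

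**What to change.** - Recalculate power for 7 PN, 6 SMS and 4 SOC clinics with a small-cluster correction, stating the degrees of freedom.
- Use the same reference for the primary test in the Analysis section (bias-corrected sandwich variance with t quantiles), so that power and analysis match.
- Say whether the ICC or the CV is the assumption and, if the CV, whether it is constant across arms. Give the PN v SMS reference rate.
- Either keep 20-23 points and state about 71-77% power v SOC, or keep 80% and state about 21-25 points, naming the basis.
- Reconcile the clinic count with Fig. 1 and amend the Discussion sentence on what the trial is powered for.

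These are changes of text and of the planned reference distribution, with no added clinics or participants. The cost is a less favourable stated power and somewhat wider primary intervals.
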